### 2.5. Recruitment

After the PCI and during admission, the nurse will recruit eligible patients and their care partners, will ask them to sign the informed consent, perform the initial assessment and organize a programmed visit after 36 weeks. A card will be provided with the date of the appointment and a telephone number for any changes.

The participants allocated to the usual care group receive the standard prescribed care and advice about medication, and lifestyle.

Both groups will be provided with written recommendations and an explanation about the standard Mediterranean diet, physical activity, stopping smoking and treatment adherence.

Before hospital discharge, all the patients will be encouraged to follow a healthy lifestyle. Stages of change strategies will be used in addition to a motivational and behavior changing interview [37,38]. Written information will be provided about risk factors, lifestyle goals, a suggested healthy menu, recommendations about the daily intake of food groups [39], and the other behavior that the intervention is targeting.

Currently, this study has recruited 95 patients.

### 2.6. Intervention

The intervention begins during the patient’s stay in hospital immediately after a coronary event. The participants from the intervention group and their partner/carer will complete a short online tutorial describing the mobile application accessed using a mobile telephone or tablet (Figure 2). They will be advised to use the application for at least 15 min per day. This time has been considered sufficient for the daily recording of data in the pilot study. The intervention will last 36 weeks. If the patient does not record data for a week, he/she receives a message through the app encouraging him to use it. The patients may resolve any queries using the application’s built-in messaging function, to which the nurse will reply through this messaging service or with a telephone call. This avoids many patient visits to the doctor for consultations and reduces human resource needs.

Before the trial, a pilot study was performed with 20 participants to test the application and make any necessary adjustments.

### 2.7. Technical Data of the Website and Application

The responsive online application (user registration, data management, downloading records) is managed via the project website, which acts as an access platform after validation with a username and password. The web environment enables the application to be executed using any browser. Operating environment: it is an application with remote access to a MySQL database. Technology development: (a) uses PHP scripting language (Personal Home Page Tools); (b) AJAX web development techniques (Asynchronous JavaScript and XML). The application runs in the user’s browser while it communicates with the server in the background; and (c) Bootstrap open-source tools for designing websites and online applications. Data storage: MySQL database is fast enough to deploy web applications. Data protection: in addition to on-demand backups performed by the software, the web server performs daily backups of all the files, so the data and program are doubly protected. Access privacy: The data are not stored in a local computer but on a web server, meaning they can only be accessed with a username and password. This web server works with anonymous data and is located in the country to comply with the regulations for the protection of high-level data.

### 2.8. Application Contents

The application allows users to set goals and monitor their food consumption, physical exercise, blood pressure, tobacco use, and compliance with their treatment. It is based on the phases of change theory (attention, retention, memory, action, and motivation) [37] and on making the process pleasing [40,41]. The user’s attention is caught through warnings and bright, attractive colors on the user interface; retention is encouraged by reminders, repetition and graphs; action is prompted by instructions, advice, and feedback; and motivation to change is boosted by internal comparisons (progress graphs), setting goals, self-monitoring and feedback.

Through its different components (website, messages, emails, and calls), participants are encouraged to (1) follow a healthy eating pattern based on the Mediterranean diet aligned with national dietary guidelines [39]; (2) perform physical activity of duration and intensity in line with the recommendations of their cardiologist; (3) stop smoking; (4) monitor their blood pressure; (5) adhere to their treatment by associating taking medication with daily activities, establishing set times for taking it and with support from a relative, etc.

### 2.9. Components of the Application

A. Provide information encouraging a healthy lifestyle. Through the website the participants will have access to information on their screens that they can print to help them plan a healthier lifestyle and adhere to their treatment. The application also has a training section for the patient with information about the recommended therapeutic objectives in the clinical practice guidelines regarding food, physical activity, body weight, blood pressure, blood sugar, stopping smoking and adhering to treatment.

B. Self-monitoring. The application has a recording and self-checking function to help patients to self-monitor the skills for each behavioral goal about nutrition, physical activity, tobacco consumption, blood pressure, body weight, capillary blood glucose in patients with diabetes mellitus and treatment adherence.

Nutrition (Figure 3). The food eaten in each meal (breakfast, lunch, tea, and dinner) is recorded using a drop-down list from which the food, and the amount consumed are selected (a portion, half portion or quarter portion). This is preferably recorded daily, or at least once a week.Physical activity and rest (Figure 3). The patient can select from a drop-down list the type of activity performed during the day, the duration, and the total number of steps each day. Additionally, they record the number of hours of sleep from the previous night and the minutes they are seated or having a siesta.Treatment (Figure 3). The participant accesses a screen with a personalized list with their daily treatment (name of medication, dose and timetable) and indicates the medication is taken, which is recorded. Medication cannot be recorded in advance.

Body weight (Figure 4). The participant records their body weight and waist circumference every week. The application calculates their BMI and classifies the value as normal, overweight, or obese, following the WHO BMI classification for adults [42]. The size in cm is recorded at the beginning when the application is activated.Blood pressure (Figure 4). The participants record their systolic and diastolic blood pressure as well as their heart rate every week.Blood glucose in patients with diabetes mellitus (Figure 4). Twice a week, the patients record their fasting blood glucose and levels two hours after consuming food.Tobacco in smokers (Figure 4). Record the number of cigarettes smoked in a week.

C. Motivate patients to improve and maintain lifestyle habits. 1. By automatic text message reminders about healthy habits generated randomly on a pop-up screen (once a week). 2. By personalized messages about reaching goals related to improving their lifestyle and treatment adherence, and recommendations about aspects to be improved. (Figure 5). The messages are produced in response to the information recorded by the patient over the previous seven days. The patients, therefore, receive weekly feedback via pop-ups that appear when the application is opened on Mondays and Tuesdays (after reading the information on the pop-up screen, it can be closed). The messages appear as short sentences in green, yellow, and red depending on the degree of compliance and control of the goals. The message is in green when the set goals have been reached; in yellow if they have partially reached; and in red when the goal is pending (Figure 5).

As a reminder of achievements and aspects to improve, on the other days of the week (Wednesday to Sunday) the top left corner of each section of the main screen of the application appears in the color corresponding to the goals reached during the previous week. (Figure 5).

### 2.10. Training Session about the Application for Patient and Carer

The nurse will install the shortcut to the application on the screen of the participant’s mobile phone and will record the prescribed treatment including the name, dose, and timetable in the application. The nurse will update the prescription in the application if the doctor changes the treatment. During the training session, the participants learn to use the functions of the application: confirm when medication is taken, record the food consumed and physical activity performed (daily), blood pressure, weight, and tobacco consumption (weekly), and capillary blood glucose in participants with diabetes mellitus (twice a week).

The participants can follow their evolution and progress through the graphics generated with the information they have recorded over the previous eight weeks (Figure 6).

### 2.11. Ethical Considerations

The study will be conducted in agreement with the guidelines and protocols established in the Helsinki Declaration as revised in Fortaleza (Brazil) in October 2013, and complies with Law 14/2007 on Biomedical Research and with European Data Protection Regulations. It was approved by the Biomedical Research Ethics Committee of the Costa del Sol, Andalusia, with the reference: 003_ene19_PI-EVITE-18. The informed written consent of all the patients will be requested. The application guarantees the security measures regarding the current General Data Protection Regulations in Europe. It also includes data encryption mechanisms.

Clinical trial number in Trial: NCT04118504.

## 3. Results

Thirty-six weeks after the initial assessment, all the patients are reassessed in terms of their lifestyle, risk factors, and treatment management. In the intervention group, the variables related to usability, and satisfaction with the application will also be appraised. The participant’s satisfaction with the treatment received will also be evaluated (using a questionnaire). Records will be taken of whether the patient has been referred to cardiac rehabilitation and their attendance. Records will also be kept of the cardiovascular events occurring during the study, the use of health services and emergency visits taken from electronic medical records.

### 3.1. Variables Collected in the Initial and Final Evaluations

All the participants are evaluated at the beginning and end of the study though an interview, checking the information given against their electronic medical records. During hospitalization, after the PCI, an assessment is performed of sociodemographic characteristics, educational level, alcohol intake, tobacco consumption, and clinical situation (history of diabetes mellitus and its complications, high blood pressure, hyperlipidemia, previous cardiovascular events, number of stents implanted, Euroscore II scale classification of the left ventricular ejection fraction (LVEF)) [43]. Body weight, height (to calculate BMI), waist circumference [42], and systolic and diastolic blood pressure (mm Hg) will be measured. An examination will be performed of plasma concentrations of LDL cholesterol (mg/dL), high-density lipoprotein (HDL) cholesterol (mg/dL), and baseline blood glucose and glycosylated hemoglobin (HbA1c) in patients with diabetes corresponding to levels in analyses performed before the intervention and after the final evaluation. Tobacco consumption will be assessed by the self-reported number of cigarettes per day and the Fagerstrom nicotine dependence test. [44,45] Stopping smoking will be self-reported and confirmed by a concentration of carbon monoxide in exhaled air of fewer than six parts per million measured with a co-oximeter CO CHECK PRO (MD Diagnostics LTD) at the beginning and end of the study. To evaluate dietary intake patterns, validated questionnaires will be used for assessing adherence to the Mediterranean diet and the frequency with which foods are consumed [33,34]. To convert the food consumed into kilocalories and nutrients, Spanish food composition tables will be used [46]. Physical activity will be evaluated using the validated Spanish version of the Minnesota physical activity questionnaire (MET min/week) [35,36]. The time (minutes/day) for sedentary activity and sleep will also be recorded. Treatment adherence will be evaluated using the Morisky–Green test [47]. Knowledge of coronary disease, CVRFs, and a healthy lifestyle will be examined using a validated questionnaire [48]. An OMS questionnaire will be used to study levels of anxiety and depression [49], quality of life [50], and well-being [51].

Usability will be evaluated in the intervention group using a 21-item questionnaire completed after the intervention to assess the user’s acceptance of mHealth inventions [52]. Satisfaction with the application will be assessed using a specific questionnaire developed by the research team.

### 3.2. Variables Recorded during the Intervention Using the Online Application

During the study period, and only in the intervention group, variables will be examined corresponding to (1) dietary intake recorded for 24 h, 7 days/week (or at least once a week). The participants select an icon corresponding to the kind of food, portions and size of the portion that they have consumed during that day; (2) minutes and type of physical activity performed, and time spent on sedentary activities and sleep. Number of steps/day using an Onwalk 100 pedometer and accelerometer (Geonaute, Decathlon, Spain), 7 days/week; (3) tobacco consumption: mean number of cigarettes/day once a week; (4) treatment compliance: treatment taken seven days/week; (5) self-measured body weight once a week to calculate BMI; (6) systolic and diastolic blood pressure measured once a week; (7) fasting and postprandial capillary glucose in patients with insulin-dependent diabetes mellitus, two times per week; and (8) frequency of use of the application (number of records per day).

#### 3.2.1. Primary Outcome Variables

The primary outcome measures after nine months in both groups will be changes in behavior relating to 1. Healthy diet: Adherence to the Mediterranean diet and average intake of each food group. 2. Level of physical activity (MET) and the number of steps per day, and a less sedentary lifestyle. 3. Smokers stop smoking. 4. Treatment Adherence. 5. Knowledge acquired. 6. Usability and satisfaction with the application.

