### 2.4. Sample Size

To detect a medium effect size of Cohen’s d of 0.5 [32] regarding adherence to the Mediterranean diet (8.6 ± 2.0 puntos) [33], food consumption, vegetables (471.4 g/day ± 230.0 g/day), fruit (308.4 g/day ± 188.6 g/day), meat and derived products (149.7 g/day ± 63.7 g/day), fish (122.3 g/day ± 73.5 g/day) [34], physical activity (210.2 METs-min/day ± 221.8 METs-min/day) [35,36] and a 12% decrease in smoking habits (prevalence of 21% in pilot study), a 95% confidence interval and a power of 90%, the sample size is estimated at 100 patients in each group. Assuming a 20% loss to follow-up with 240 participants, 120 in each arm: intervention and usual care.

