### 3.3. Statistical Analysis

The principles of intention-to-treat analysis will be followed. The differences between patients who gave up the app and those who were able to utilize it will also be examined by analyzing the outcome variables from the electronic medical record. A descriptive statistical analysis will be performed (mean, standard deviation, 95% confidence interval, frequencies, and percentages). For the comparison of means, the Student’s t-test will be used (normal distribution variables) and the Mann–Whitney U test (if the variables are non-normally distributed). The Chi-squared/Fisher test will be used for the comparison of proportions. The relative risks and 95% confidence intervals will be computed. The quantitative primary outcomes from the two groups will be compared using an analysis of covariance adjusted for age and gender. A sensitivity analysis will also be performed regarding the baseline characteristics of the participants in both groups and missing data. A multivariate analysis will be performed to examine the association of the intervention with lifestyle habits, control of the CVRFs and evolution after discharge regarding cardiovascular events, the use of health services, emergency visits, and readmissions using Kaplan–Meier survival analysis. A two-tailed *p*-value < 0.05 will be considered statistically significant. The SPSS v.24.0 software will be used. 24.0. The researchers analyzing the results will be blinded to the allocation of the participants.

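### At least ten unranked between-arm primary variables share one flat 0.05 threshold, with no rule for which result decides the trial

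*Protocol article*

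**What the plan says.** Section 3.2.1 (Primary Outcome Variables) numbers six domains, all primary at nine months: diet, physical activity, smoking cessation, treatment adherence, knowledge, and usability and satisfaction with the app. Several hold more than one variable. The diet domain alone reads "Healthy diet: Adherence to the Mediterranean diet and average intake of each food group", and the activity domain names MET, steps and sedentary behaviour. No domain or variable is placed ahead of the others.

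Section 2.4 (Sample Size) begins "To detect a medium effect size of Cohen’s d of 0.5" and applies this to the Mediterranean-diet score, four food groups, such as "vegetables (471.4 g/day ± 230.0 g/day" and "fish (122.3 g/day ± 73.5 g/day", and physical activity. It adds a decrease in smoking. That makes seven outcomes sized together, with no lead among them.

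Section 3.3 (Statistical Analysis) compares the quantitative primary outcomes by ANCOVA and sets one general rule: "A two-tailed *p*-value < 0.05 will be considered statistically significant". It does not say how many primaries must succeed, in what order they are tested, or whether the threshold is shared among them.

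**The concern.** With many co-equal primaries and one unshared threshold, a reader of the final report cannot tell which result decides whether the app works. A nominally significant difference in one food group could be presented as a significant primary result while the diet score, activity, smoking and treatment adherence showed nothing. On that use of the results, the 5% error rate holds for each test but not for the conclusion drawn from the set. The sample size has the same gap: its power statement relates to individual outcomes, and nothing says which of them the 90% is meant to protect.

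**Working it through.** **The plan's own figure.** The article states no family-wise error rate, so the only figure to reproduce is 100 per arm. For d = 0.5, two-sided 0.05 and 90% power, n = 2(1.960 + 1.282)²/0.5² = 84.1, so 85 per arm (86 by the exact t-test). This does not give 100; with 100 per arm, power at d = 0.5 is 94%. That mismatch is a separate matter and does not affect this point. After the stated 20% loss, 120 × 0.8 = 96 per arm are analysed, with 93% power at d = 0.5.

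**Counting the between-arm primary variables.**
- Mediterranean-diet score: 1 (section 3.2.1)
- Food groups: at least 4, those named in section 2.4 (vegetables, fruit, meat, fish)
- MET: 1
- Sedentary time: 1 (section 3.1 records it for all participants)
- Smoking, treatment adherence, knowledge: 3

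Total: 1 + 4 + 1 + 1 + 3 = 10. Steps are left out because section 3.2 records them only in the intervention group. Usability and satisfaction with the app are left out because they exist only for app users. Because section 3.2.1 speaks of every food group, ten is a minimum.

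**Chance of at least one false positive.** For k independent tests at 0.05 with no true effect, the chance is 1 − 0.95^k. For k = 10 this is 1 − 0.95¹⁰ = 0.401. For test statistics with a common correlation ρ, it is one minus the probability that all k jointly normal statistics lie within ±1.96, obtained by numerical integration. The article gives no correlation, so a range is shown:

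| Tests | ρ = 0 | ρ = 0.3 | ρ = 0.5 | ρ = 0.7 |
|---|---|---|---|---|
| 5 (one per between-arm domain) | 22.6% | 20.9% | 18.3% | 14.8% |
| 10 (named variables) | 40.1% | 35.1% | 28.7% | 21.3% |
| 15 (more food groups) | 53.7% | 45.7% | 36.1% | 25.6% |

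A less uniform pattern for the ten tests, with correlation 0.3 to 0.5 inside the diet and activity blocks and 0.1 elsewhere, gives 38.1% to 35.9%.

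**Power if the threshold is shared.** Holm compares the smallest of ten p-values with 0.05/10 = 0.005. At that level and d = 0.5, power for a single outcome is 73% with 96 per arm and 76% with 100. Reaching 90% at 0.005 needs 2(2.807 + 1.282)²/0.5² = 133.7, so 134 per arm (136 by t-test). That exceeds the 120 to be randomised per arm.

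**The case against.** **The decision rule is inferred.** This is the strongest objection, and it stands. A reader might infer that, followed as written, any single significant food group makes the trial positive, with an error rate of 30–40%. The article does not say so: it states neither an any-one rule nor an all-must-succeed rule. If every primary had to succeed, the error would not be inflated this way. If each behaviour were reported separately with no overall claim, these figures would not describe the trial's conclusion. They are therefore conditional, and they also assume no effect on any outcome. The range 30–40% is itself too narrow: ten tests give 21% to 40% over the correlations shown, and other counts go lower or higher.

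**The statistical analysis plan may settle it.** Details of a multiplicity procedure may well be there, and their absence from the article is not the finding. But the article itself fixes unranked primaries and one threshold. A later plan that named a lead outcome would change section 3.2.1. One that split the 0.05 would change the threshold in section 3.3 or the power claimed in section 2.4.

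**The sample size.** A reader might infer that section 2.4 assumes 5% for each of the ten. It covers only seven; sedentary time, treatment adherence and knowledge are not sized.

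**Smoking.** Cessation concerns smokers only: at 21% prevalence, about 96 × 0.21 = 20 per arm. Fisher's test on so few is conservative, with a true size of about 2–2.5% if quit rates are 30–50% (assumed). This lowers the ten-test figure only from 40% to about 38%.

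**Conclusion.** The point holds in conditional form. Section 3.2.1 fixes at least ten between-arm primary variables with none ranked, section 3.3 fixes a single two-sided 0.05, and no stated rule links the two to a conclusion about the app. If one significant primary is treated as sufficient and there is no true effect, the false-positive chance is 40% for ten independent tests and 21% at a correlation of 0.7. Counting only the five between-arm domains gives 15–23%, and 15 tests give up to 54%. None of these counts brings it back to 5%. The count comes from the document; the correlations, the absence of any effect and the any-one rule are assumptions. The defect bears on the trial's main conclusion and should be corrected before the data are examined by arm.

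**What to change.** Before any unblinded look, take one of two routes.

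1. **One lead outcome.** The team designates one primary outcome, tests it at two-sided 0.05 and makes the other behaviours secondary. The choice belongs to the team. The Mediterranean-diet score is one candidate: it is already sized, with 93% power at d = 0.5 and 96 per arm. Being listed first is not a scientific reason to choose it, however, and treatment adherence is also part of the stated aim. If treatment adherence is chosen, section 2.4 needs a sizing for it, since it has none now.

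2. **Several primaries.** List them explicitly, including which food groups count, apply Holm across the list and restate the power in section 2.4. With ten, power at the strictest step is about 73% with 96 per arm or 76% with 100 for d = 0.5, rather than the stated 90%. A shorter list loses less.

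Either route changes sections 3.2.1 and 3.3, and the second also changes 2.4. It requires a dated, justified protocol and registry amendment in a trial that had already recruited 95 patients when the article was written. The price is loss of primary status for some outcomes under the first route, or a lower stated power under the second. Neither route requires more patients unless the team wants to keep 90% power at the stricter level.

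### The 90% power claimed for smoking is set on prevalence in all patients, the declared outcome is cessation among about 20–25 smokers per arm, and the claim holds on neither scale as written

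*Protocol article*

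**What the plan says.** Section 3.2.1 of the Protocol article lists, as the third of six primary outcome items at nine months, "Smokers stop smoking". Section 3.1 says that stopping is self-reported and confirmed by exhaled carbon monoxide (CO) at the start and end of the study.

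Section 2.4 sets the sample size jointly for several outcomes. The continuous ones use Cohen's d of 0.5. The smoking component reads "a 12% decrease in smoking habits (prevalence of 21% in pilot study"). The result for all of them is given as "a 95% confidence interval and a power of 90%, the sample size is estimated at 100 patients in each group". The allowance for loss follows: "Assuming a 20% loss to follow-up with 240 participants, 120 in each arm". Section 3.3 fixes the test level: "A two-tailed *p*-value < 0.05 will be considered statistically significant".

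The eligibility criteria (2.3.1, 2.3.2) do not require participants to smoke. Section 2.5 gives the control arm active advice: "Both groups will be provided with written recommendations and an explanation about the standard Mediterranean diet, physical activity, stopping smoking and treatment adherence". It also describes a motivational and behaviour-change interview for all patients before discharge.

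**The concern.** The two sections use different denominators. A prevalence of 21% that falls by 12% describes all patients in a group. Smokers who stop are counted among those who smoked at baseline, roughly a fifth of the sample. The article states no quit rate, no difference in quit rates and no expected number of smokers, and nothing converts one scale to the other.

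This is more than detail left to a later analysis plan. The sample-size basis and the primary outcome are both stated in the article, and they do not match. A reader would take the trial to have 90% power for its declared smoking outcome. If it does not, a null smoking result could be read as evidence of no effect when the comparison was too small for moderate differences in quitting.

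**Working it through.** **Inputs from the article.** Prevalence 21%, decrease 12%, power 90%, 100 per group, 120 enrolled per arm, 20% loss (2.4); two-sided 0.05 and chi-squared/Fisher tests (3.3); 1:1 allocation (2.2); a pilot of 20 participants (2.6). Section 2.4 does not say whether 12% is absolute or relative. The absolute reading, 21% versus 9%, is the more favourable to the plan and is used below.

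**Assumed.** Control quit rates among smokers of 20–40%, because the article gives none.

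**1. Where the 100 per group can come from.** For d = 0.5 at 90% power, n = 2(1.96 + 1.2816)²/0.5² = 84.1, so 85 per group (86 by the t-test). Dividing by the Mann–Whitney minimum efficiency gives 86/0.864 = 99.5, about 100, although 2.4 mentions no such step. The figure of 100 can therefore come from the continuous outcomes.

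**2. Smoking over all patients, 21% versus 9%.** The mean proportion is 0.15.
- n = [1.96·√(2·0.15·0.85) + 1.2816·√(0.21·0.79 + 0.09·0.91)]² / 0.12²
- = (0.9898 + 0.6380)² / 0.0144 = 184 per group.
- Variants at 90% power: 201 with continuity correction, 179 by arcsine, 150 one-sided. At 80% power, two-sided: 138.
- Power at 100 per group: Φ[(0.12·√100 − 0.9898)/0.4978] = Φ(0.42) = 66%. At the 96 who remain after 20% loss from 120, it is 65%.
- Relative reading, 21% versus 18.5%: 5,241 per group.

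None of these reproduces 100 per group at 90% power.

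**3. Number of smokers.** 0.21 × 120 = 25.2 per arm enrolled; × 0.8 = 20.2 after loss. In a pilot of 20, a prevalence of 21% is about 4 people (4/20 = 20%, 4/19 = 21%), so this count is uncertain if that pilot is the source.

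**4. Effect implied among smokers.** If the fall from 21% to 9% arises wholly from baseline smokers quitting, the quit-rate difference is 0.12/0.21 = 57 points. With no control quitting, 57% of intervention smokers must quit. With 30% of controls quitting, control prevalence is 0.21 × 0.70 = 14.7%. The intervention arm must then reach 2.7%, which means 1 − 0.027/0.21 = 87% quitting.

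**5. Power with 20 smokers per arm** (sum over both binomial distributions, two-sided 0.05):

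| Quit rates, control vs intervention | Chi-squared | Fisher |
|---|---|---|
| 20% vs 77% | about 97% | about 94% |
| 30% vs 87% | about 98% | about 95% |
| 30% vs 60% | 46% | 35% |
| 20% vs 32% | 14.1% | 8.0% |
| 30% vs 42% | 12.5% | 7.3% |
| 40% vs 52% | 10.6% | 6.1% |

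With 25 per arm, before any loss, the normal approximation gives 57% for 30% versus 60% (48% at 20 per arm) and 13–16% for a 12-point difference. The 95% confidence half-width for the difference at 20 per arm, for 30% versus 42%, is 1.96·√[(0.30·0.70 + 0.42·0.58)/20] = 0.295, about 30 points.

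**The case against.** A reader might infer that so few smokers cannot answer the smoking question at all, and quote the 11–14% power as the trial's power. The documents do not support that. The 12% stands next to a prevalence, and the article never states a 12-point difference in quit rates. Carried over to smokers, the article's own effect is about 57 points, for which 20 smokers per arm have about 97% power or more. Restricting to smokers concentrates the effect, so for the same underlying change the smokers-only comparison has more power than the all-patient one (66%). That part of the objection stands.

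It is also fair that cessation among smokers is a clear question with CO confirmation, and that tobacco use is assessed in everyone at both visits, so either estimate can be produced. The all-patient scale is not the safer choice, since it misses 90% as well.

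Two inputs are readings rather than text: that the 21% is a baseline figure, and that it serves as the control rate at follow-up. If controls also quit and the 12-point gap is kept, all-patient power at 100 per group rises: 86% with 30% of controls quitting (14.7% versus 2.7%) and 93% with 40% (12.6% versus 0.6%). The last case needs 1 − 0.006/0.21 = 97% of intervention smokers to quit, so it does not make the claim credible.

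The objection does not remove the mismatch. The article states a power for one quantity and declares another as primary.

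**Conclusion.** The concern holds in this form: section 2.4 does not support the smoking outcome declared in 3.2.1, and its 90% figure holds on neither scale as written. Over all patients, 100 per group gives about 66% and 184 would be needed. Among smokers no effect is stated. The implied one is very large, given that usual care also includes stop-smoking advice. Smaller differences are poorly covered: about 46% power at 30 points and 11–14% at 12 points.

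This rests on the absolute reading of 12%, on trial prevalence resembling the 21%, on the change coming from smokers quitting, and on the assumed control quit rates. The point concerns one of six primary items and the power stated for it. It does not show that the smoking comparison is worthless.

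**What to change.** In 2.4 and 3.2.1, state one smoking outcome with its denominator. Keeping the declared one would mean CO-confirmed cessation at nine months among baseline smokers. Give the expected number of smokers per arm, with a range because the 21% may rest on very few people, and the assumed control quit rate, the absolute difference and the actual power. Remove the statement that 100 per group gives 90% power for smoking, and say whether 12% is absolute or relative. Report the other scale as supportive, with a 95% confidence interval.

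Moving smoking out of the primary set, or switching to all-patient prevalence, are options with trade-offs rather than necessary corrections. A switch would let non-smokers dilute the contrast and would still not deliver 90% power.

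The cost is wording and a short recalculation. No new data are needed, because smoking and exhaled CO are already measured at both visits. The downside is that the stated power for smoking becomes less favourable.
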